### Ethics review and informed consent

The study protocol was reviewed and approved by the Human Subjects Ethics Sub-committee of The Hong Kong Polytechnic University (HSEARS20120920001). In the recruitment phase, before the randomization, all the next-of-kin of subjects screened to be eligible are informed of the details of the study, including intervention and data collection procedures, potential risk and benefits. All eligible subjects are likewise informed of the same details. The subjects and the next-of-kin are clearly told about the equal chance of allocation to any one of the three groups before signing the informed consent. Subjects are recruited when 1) they sign the written informed consent (if they are sufficiently cognitively sound) or assent to participate (that is, nodding, verbalizing, or not rejecting when acupressure is performed on them), and 2) the next-of-kin sign the written proxy consent [42]. Due to the principle of blinding, only the participants allocated to the usual-care group will be told to wait for their free compensatory acupressure treatments after completion of the study. The group allocation status will be strictly concealed to the participants, next-of-kin, data collectors, and nursing home staff throughout the study period. The group allocation will only be revealed after completion of the study.

### Statistical methods

#### Sample size estimation

To estimate the sample size using G*Power® [43], with assumptions (that is, α =0.05, power =0.8, three groups), estimated effect size (that is, f =0.27) and attrition rate (that is, 10%) from the pilot study [32] and the previous similar studies [26, 27], the total number of samples needed in a randomized controlled trial to demonstrate a significant mean difference among the three groups is 99. There will therefore be 33 participants in each group.

#### Analysis

Data analysis will be performed by a statistician blinded to the whole trial process using IBM SPSS Statistics 20 software [44]. The level of significance will be reported at *P* <0.05. Both per-protocol and intention-to-treat analysis will be used in order to provide more information on the effect of the intervention, considering possible confounders such as non-compliance, protocol deviations and withdrawal [45]. The per-protocol population is defined as participants who completed the study without major protocol violation (for example, who received more than 80% of the acupressure sessions). The intention-to-treat population is defined as participants who are randomized into groups after the collection of baseline data. Demographic and clinical data will be analyzed at baseline to measure the balance among the three groups. The results will be described by mean and standard deviation for continuous data, and by frequency and percentage for categorical data. The general estimated equation model will be used to compare the effects among groups and time points.

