**Methods/design:**

This study is a multicenter, assessor/participant/statistician-blinded, parallel group, randomized controlled trial taking place in Hong Kong nursing homes. We have been recruiting PWD over 65 years of age in nursing homes, who are experiencing agitation; 99 participants will be recruited in order to demonstrate a significant effect difference (that is, f =0.27) with a power of 0.8 and a significance level of 0.05 among the three groups. Participants are assigned by permuted block randomization into three groups in a 1:1:1 ratio. In the acupressure group, participants receive acupressure at the Fengchi (GB20), Baihui (GV20), Shenmen (HT7), Niguan (PC6) and Yingtang (EX-HN3) acupoints. In the sham-acupressure group, participants receive pressure on five non-acupoints. In the usual-care group, participants receive no intervention apart from the care provided by the nursing homes. Participants assigned to the sham-acupressure and usual-care groups receive free acupressure, like those in the acupressure group, after completion of the study. The whole study lasts for 30 weeks, and its primary outcome measure is agitation. The general estimated equation model will be used to compare the effects among groups and time points. The trial is currently recruiting participants.

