### Recruitment procedures

We have invited all the RCHs in Hong Kong that are registered under the Social Welfare Department and fulfill the following criteria: (1) they have more than 100 beds; and (2) they provide beds for moderate/severe functioning elders (that is, Care and Attention Homes and Nursing Homes) [31]. The RCHs are invited by mail and followed up by telephone. Of the RCHs who were interested in participating, 12 RCHs were selected randomly to launch this study. Only 12 were selected because it was estimated from the pilot study [32] that at least 12 RCHs with more than 100 beds each would provide sufficient participants for the study (that is, 99 participants). Within the 12 selected RCHs, our research team is working closely with RCH staff to screen all the residents against the selection criteria. After screening, all eligible residents are invited to participate in the study by telephone. Participants are included only if they meet the selection criteria and provide assent/informed consent, and if the next-of-kin provide written informed proxy consent (Figure 1).

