### Blinding

Participants, next-of-kin, data collectors, nursing home staff (that is, the formal caregivers providing the Cohen-Mansfield Agitation Inventory (CMAI) data and the nurses administering the psychotropic drugs), physicians prescribing the psychotropic drugs, and the statistician will be blinded to the group allocation status; however, blinding is clearly not possible in the usual-care group. The group allocation status will only be revealed after completion of the study.

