### Outcome measurement

The primary outcome in this study is the change of agitation (that is, CMAI score), and the secondary outcome is the change in stress ( measured by salivary cortisol concentration). The outcomes will be measured at the baseline (T0), the week immediately after completion of the intervention (T1), 2 weeks after completion of the intervention (T2), and 6 weeks after completion of the intervention (T3). The measurement at T1 aims to examine the immediate effect after the intervention, that at T2 aims to examine the peak effect, and that at T3 aims to examine the delayed effect. The decision to use the measurement interval of T2 and T3 was based on the result of the pilot study [32], where weekly repeated measurement showed that the effect of acupressure peaked at the time point 2 weeks after the completion of intervention and diminished to very close to baseline at the time point 6 weeks after the completion of intervention.

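### The primary comparison is in effect a change-score contrast; using baseline CMAI as a covariate would give a more precise estimate from data already collected

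*Protocol article*

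**What the plan says.** Under Outcome measurement, the primary outcome is the change in CMAI score and the secondary outcome is the change in salivary cortisol. The same section states "The outcomes will be measured at the baseline (T0") and goes on to list T1, T2 and T3, which fall in the week after the intervention and 2 and 6 weeks after it. T1 is meant to show the immediate effect, T2 the peak and T3 the delayed effect.

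Under Analysis, the model is given in one sentence: "The general estimated equation model will be used to compare the effects among groups and time points". Otherwise that section mentions baseline in two places. Baseline characteristics are to be summarised to judge balance, and the intention-to-treat population is made up of participants randomised once their baseline data are in.

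Under Sample size estimation, the inputs are "α =0.05, power =0.8, three groups", an "estimated effect size (that is, f =0.27") and an "attrition rate (that is, 10"%), which lead to 99 participants, 33 per group. Neither the test nor a correlation between repeated measurements is stated.

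**The concern.** The outcome is change, T0 is one of the times, and the factors compared are groups and times. The treatment effect at a visit is then the group-by-time term: how far one group moved from T0, less how far another moved. With complete data and a free mean for every group at every time, the GEE estimate of that term is the difference in mean changes whatever working correlation is chosen. The correlation structure therefore does not recover the information in the baseline.

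A change score subtracts the whole of the baseline value, whereas the best linear prediction of follow-up subtracts only rho times it (equal variances). Two things follow when rho is below 1:

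- The contrast carries extra noise, so standard errors are larger than they need be.
- If the groups differ at baseline by chance by an amount D, the change score over-corrects by (1 - rho) x D. With 33 per group, some imbalance is to be expected.

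At stake is precision in the trial's main result, and especially in the visit-specific contrasts, since each visit has been given its own purpose.

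**Working it through.** **Inputs from the article.** alpha = 0.05, three groups, f = 0.27, attrition 10%, 99 randomised. Evaluable: 99 x 0.9 = 89.1, taken as 90 (30 per group). With 89 the powers below change by less than one percentage point.

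**Assumptions.** rho between baseline and follow-up CMAI is not given, so 0.3, 0.5 and 0.7 are shown. Raw-score variance is set to 1 at each time, and f = 0.27 is taken in raw-score standard deviations.

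**The article's own figure.** Power is from the noncentral F distribution.
- As a one-way comparison, lambda = N x f^2. Power of 80% needs 136, or 138 in equal groups, and 138/0.9 gives 154 recruited. This is not 99.
- As a repeated-measures between-groups test over four times with rho = 0.5, lambda = N x f^2 x 4/(1 + 3 x 0.5). This needs 86, or 87 in equal groups; 87/0.9 = 96.7, so 97, and 99 in equal groups. This agrees with the article, but both the test and rho are inferred.

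**Variance of the single-visit contrast.**
- Change score: 1 + 1 - 2 rho = 2(1 - rho)
- Baseline as covariate: 1 - rho^2
- Ratio: (1 - rho^2)/[2(1 - rho)] = (1 + rho)/2

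The ratio is below 1 for every rho below 1.

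**Power.** lambda = 90 x 0.27^2/variance = 6.561/variance, with 2 and 87 degrees of freedom.

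| rho | Variance, change | Variance, adjusted | Ratio | lambda, change | lambda, adjusted | Power, change | Power, adjusted |
|---|---|---|---|---|---|---|---|
| 0.3 | 1.40 | 0.91 | 0.65 | 4.69 | 7.21 | 46% | 65% |
| 0.5 | 1.00 | 0.75 | 0.75 | 6.56 | 8.75 | 61% | 74% |
| 0.7 | 0.60 | 0.51 | 0.85 | 10.94 | 12.86 | 84% | 89% |

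The degree of freedom spent on the covariate is negligible: at rho = 0.5, power is 74.2% with 86 denominator degrees of freedom and 74.3% with 87.

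**Does the gain depend on looking at one visit?** Average T1 to T3, with the same rho between all pairs of times. The mean of three visits has variance (1 + 2 rho)/3. The change variance is (1 + 2 rho)/3 + 1 - 2 rho, and the adjusted variance is (1 + 2 rho)/3 - rho^2. At rho = 0.5 these are 0.667 and 0.417, ratio 0.625; at rho = 0.7 they are 0.400 and 0.310, ratio 0.775. The relative gain is larger than at one visit. Absolute power is also higher: 79% against 95% at rho = 0.5.

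**The case against.** **A single sentence in a condensed article is not a model specification.** Covariates are commonly left to an analysis plan, and one that adjusts for baseline may exist. This has force: the article does not say that baseline adjustment is ruled out. But it does more than stay silent. It names the outcome as change, includes T0 among the times and names the factors compared, and together these describe a particular estimator. If a fuller plan already adjusts, the point is met by saying so.

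**Change score against covariate is a choice between two valid analyses.** True. Neither is biased under randomisation, and nothing here inflates the type I error. The case is efficiency alone.

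Three stronger readings are tempting, and the documents do not support them.

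- *That baseline CMAI is missing from the analysis.* It enters through the change outcome and the T0 time point. The issue is how it enters.
- *That the trial is underpowered.* The total of 99 can be reproduced with a four-measurement between-groups test at rho = 0.5. It falls short on a one-way reading, but the article does not say which test was used. The powers in the table are for one visit under assumed correlations and are not the planned power of the whole model. At rho = 0.7 even the change score exceeds 80%.
- *That a nursing-home term, or blocking within home, is wrongly left out.* The article says that "12 RCHs were selected randomly to launch this study", and its Blinding section identifies "the formal caregivers providing the Cohen-Mansfield Agitation Inventory (CMAI) data" as nursing home staff, so residents of one home may share raters. But the absence of a home term or of stratification is only silence in a condensed article, and no intracluster correlation is given. A stable home effect also largely cancels from a change score. Altering the blocking during recruitment, or replacing the GEE with a mixed model, would not be free.

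**Conclusion.** The point holds as one of precision. The analysis described is a change-score contrast, and conditioning on baseline would reduce the variance of the single-visit contrast by 35%, 25% and 15% at rho of 0.3, 0.5 and 0.7. Under the stated assumptions, that is worth 19, 13 and 5 percentage points of single-visit power.

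The variance ratio rests on randomisation, equal variances over time and a linear relation between baseline and follow-up. The power levels rest also on rho, which the article does not give, and on f being in raw-score units. If f was instead derived on the change scale, the power levels would shift but the variance ratio would not.

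**What to change.** Keep the GEE and change what it conditions on. Take CMAI at T1, T2 and T3 as the responses, with group, visit and group-by-visit as terms and baseline CMAI and baseline-by-visit as covariates. Report the group contrasts at each visit from that model. Treat salivary cortisol in the same way, with baseline cortisol. Change from baseline can still be shown descriptively.

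The cost is a sentence or two of analysis wording. Both outcomes are already measured at T0, and the intention-to-treat definition places randomisation after baseline collection, so the covariates should be close to complete. A participant with no follow-up visit adds nothing to this model, but would add nothing to a change score either. The trial is still recruiting and allocation is to stay concealed until the study is complete, so the wording can be settled before unblinding. If an existing analysis plan already specifies this, a statement to that effect is enough.

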## Discussion

The results of this study will primarily answer the question whether acupressure demonstrates a significant effect in a tightly controlled trial (with maximum possible blinding and stringent control of the intervention implementation fidelity). One of the key active components of acupressure, differentiating it from other manipulative therapies (for example, massage, therapeutic touch), is the activation of acupoints. This study first provides a sham-acupressure group to compare the efficacy difference of acupressure between tactile stimulation and acupoint stimulation. This study uses a relatively shorter intervention duration. A shorter duration of therapy may favor greater compliance with the intervention in the clinical application. This study is the first to use a bio-marker (that is, salivary cortisol) and the extent of the use of psychotropic drugs to track the outcome of the intervention. These may provide a more objective comparison of effects. Finally, this study is also the first to examine the delayed effect of the intervention. This may also provide a reference for clinical application.

## Trial status

The trial is currently recruiting participants.

## Abbreviations

AG: acupressure group
CMAI: Cohen-Mansfield Agitation Inventory
PWD: people with dementia
RCH: residential care home
TCM: traditional Chinese medicine.
